##### Exercise enjoyment

The Portuguese version of the Physical Activity Enjoyment Scale (PACES) (Bastos et al., 2025b) will be used to assess enjoyment of exercise. This instrument contains 18 items using a 7-point bipolar scale (e.g., “It’s no fun at all – It’s a lot of fun”).

##### Affective exercise experiences

The attraction-antipathy and the pleasure-displeasure scales of the Affective Exercise Experiences Questionnaire (AFFEXX) (Ekkekakis et al., 2021) will be used. The first scale is a motivational outcome variable consisting of five items assessing the tendency to approach or avoid exercising (e.g., “Exercise is low on my priority list—Exercise is high on my priority list”); the second, is a core affective experience assessment, evaluated with four items (e.g., “Exercise makes me feel worse—Exercise makes me feel better”). Both are answered on a 7-point bipolar scale. A translation and back-translation of the full questionnaire was performed following several recommendations for adequate instrument translation and adaptation (Brislin, 1970; Brislin, 1980) and has been used in the context of exercise in fitness clubs [e.g., (Teixeira et al., 2023)].

##### Intensity preference/tolerance

Preference for and tolerance of exercise intensity, and their agreement with individually experienced intensity, will be assessed using the Portuguese version of the Preference for and Tolerance of Exercise Intensity Questionnaire (PRETIE-Q) (Teixeira et al., 2021). The instrument is composed of 10 items (five for each factor; preference: “While exercising, I prefer activities that are slow-paced and do not require much exertion”; tolerance: “I always push through muscle soreness and fatigue when working out”) answered on a 5-point Likert scale ranging from 1 (“Totally disagree”) to 5 (“Totally agree”). The two additional items included in this version of the instrument to assess exercise intensity preference (“The intensity of my workout is in agreement with my preference”) and tolerance (“The intensity of my workout is in agreement with my tolerance”) will also be used to evaluate participants’ perceptions of the prescribed workout intensity relative to their individual preferences.

##### Exercise habit

The Portuguese version of the Self-Report Behavioral Automaticity Index (SRBAI) (Rodrigues et al., 2021) will be used to measure exercise-related habit formation. This scale contains four items (e.g., “I do [it] without thinking”), answered on a 7-point Likert scale ranging from 1 (“Totally disagree”) to 7 (“Totally agree”).

##### Intention to be physically active

Behavioral intention will be measured using a single item: *“I will continue to practice physical exercise in the next 6 months as I recently practiced or in a very similar way (same type, frequency, duration, and intensity),”* based on previous studies in the Portuguese context (Teixeira et al., 2021) and grounded in Ajzen’s (2006) theoretical work. Responses are given on a 7-point bipolar scale ranging from 1 (“Absolutely not”) to 7 (“Absolutely yes”).

##### State self-control

The Portuguese version of the Brief Self-Control Scale (BSCS) (Pechorro et al., 2018) will be used to assess trait self-control. The instrument includes 13 items (e.g., “It is hard for me to break bad habits”), reflecting a unidimensional construct. Responses are given on a 5-point Likert scale ranging from 1 (“Totally false”) to 5 (“Totally true”).

##### Club attendance and attrition rate

Attendance data will be obtained through the electronic system that tracks the entrances and exits from the turnstile systems of the clubs. These data will be collected for the entire season (September – August) for all members, when the following condition is present: (a) active payment + (b) a minimum of 1 attendance per month^1^. The attrition rate will be calculated for each 3-month period and the entire season with the following formula: Attrition Rate = (Number of Cancellations or Dropouts / Total Number of Members) × 100. New club members who enrolled in the fitness clubs after September 1, 2025, will also be identified separately for subgroup analysis.

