### Outcomes

The primary outcome variable will be club attendance, which, for the designated fitness centers, will only reflect club visits with the intent to exercise and not access complementary services (i.e., spa, well-being centers, coffee lounges). This will be assessed across all trimesters, with particular emphasis on one-year results (as the primary outcome endpoint). Comparisons will be made over time within and across intervention conditions for both new members enrolling between September 1, 2025, and August 31, 2026, and members already enrolled prior to this period, for whom the intervention may reflect a change from their prior club experience. The secondary outcomes will be behavioral (attrition rate, namely the number of membership cancellations or dropouts as a percentage of the total number of new members in a given time period; see Methods section for details) and motivational constructs (exercise habit, intention to be physically active, satisfaction of basic psychological needs, behavioral regulation, enjoyment, and affective exercise experiences), in line with the study’s secondary hypotheses regarding potential motivational and behavioral changes associated with the intervention conditions. These will be assessed in a subsample of participants who will voluntarily take part in the longitudinal evaluations. Additional variables (i.e., state self-control, intensity agreement, course content evaluation, one-year pre-intervention attendance, and attrition patterns at the club level, and the degree and frequency of application of the knowledge provided during the training course) will be included for descriptive or exploratory tertiary analyses. No harm is expected from the intervention.

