### Sample size

Sample size determination follows SPIRIT (Chan et al., 2025) guidance for pragmatic interventions in which traditional power calculations are constrained by design features. As such, considerations were made while considering the nature of the intervention, the fitness-center–level allocation of training conditions, and the longitudinal structure of the primary outcome. Given that only three centers are included, formal power calculations for between-condition hypothesis testing based on individual-level randomization are not appropriate. Instead, sample size adequacy is primarily related to the large number of individual observations and repeated measurements, which support the longitudinal estimation of attendance trajectories over time within the constraints of the present pragmatic design.

For the primary outcome (attendance), all eligible members of the participating fitness centers will be included in the analyses at three, six, nine, and 12 months, although the focus will be given to those enrolled after September 1, 2025. Each participating fitness center has more than 2,000 enrolled members at any given time, and historical records indicate that approximately 200 new members typically enroll in each club during the month of September. This provides a high-density longitudinal dataset, with multiple repeated observations per individual and sufficient sample size in each intervention condition to support longitudinal mixed-effects modeling of attendance trajectories.

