### Statistical methods

Preliminary analyses will be conducted prior to all statistical procedures to examine data quality, missingness patterns, and identify potential violations of statistical assumptions. All analyses are planned to be performed using SPSS v.27.0 (IBM, Co.). The primary outcome of the study is attendance, which will be analyzed both for all fitness center members and separately for those who joined the clubs after the commencement of the study (i.e., after September 1, 2025). Attendance will be operationalized as the individual’s mean weekly attendance within each three-month interval and assessed at four time points during the 12 months of the study (three, six, nine, and twelve months). Primary analyses of attendance will be conducted using linear mixed-effects models (LMMs), with time specified as a within-subject factor and individuals treated as random effects to account for repeated observations. Intervention condition (control, SDT-based training, and hedonic-based training), time, and their interaction will be included as fixed effects, with age and sex included as covariates. These models will be used to characterize and descriptively compare attendance trajectories over time across intervention conditions, with emphasis on the magnitude and direction of longitudinal patterns rather than on individual-level causal inference. Primary analyses will follow an intention-to-treat principle adapted to the cluster-allocated design, such that all eligible individuals are analyzed according to their fitness center’s assigned condition, regardless of attendance patterns or dropout. Linear mixed-effects models were selected because they incorporate all available longitudinal observations under a missing-at-random assumption without requiring imputation.

Because intervention allocation occurs at the fitness-center level and each condition is implemented in a single center, cluster-level variance and intraclass correlation coefficients cannot be estimated independently of condition-related effects. Accordingly, comparisons across intervention conditions are considered exploratory and descriptive in nature. For complementary descriptive purposes, 3 (Condition) × 4 (Time Points) split-plot ANOVAs may be conducted to summarize overall patterns of longitudinal change in attendance. Results from these analyses will be interpreted descriptively, given that intervention conditions are implemented at the fitness-center level.

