Secondary outcomes include dropout and motivational variables. Dropout (membership cancellation) will be examined using administrative records from all members enrolling after September 1, 2025. Dropout rates will be summarized at three-month intervals, and time-to-event analyses will be used to describe adherence patterns over the 12-month period. Percentage attrition rates will be reported descriptively, and Kaplan–Meier survival curves will be used to illustrate the timing of dropout across conditions. Participants who remain actively enrolled at the end of the observation period will be treated as censored observations at their last available follow-up time point. Motivational and behavioral variables will be analyzed in the longitudinal subsample of participants. Changes over time in these variables (baseline, six, and twelve months) will be examined using linear mixed-effects models, with time specified as a within-subject factor and participants treated as random effects. Intervention condition, time, and their interaction will be included as fixed effects, with age and sex entered as covariates. Given the limited number of repeated measurements, models will be specified with a parsimonious random-effects structure. For consistency with prior literature and ease of interpretation, complementary 3 (Condition) × 3 (Time Points) split-plot ANOVAs may also be conducted, with results interpreted descriptively. Effect sizes will be reported as model-based estimates of change over time (e.g., differences in attendance slopes and estimated marginal means), with 95% confidence intervals. Additional control, complementary, and exploratory analyses are anticipated, particularly within ancillary studies.

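### Primary attendance data are kept only for members with at least one visit per month, so the outcome is selected on its own value, against the stated intention-to-treat rule

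*Protocol article*

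**What the plan says.** Outcomes states: "The primary outcome variable will be club attendance". Statistical methods measures it as each individual's "mean weekly attendance within each three-month interval", at 3, 6, 9 and 12 months, in a linear mixed model that relies on a missing-at-random assumption.

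Club attendance and attrition rate (under Data collection methods) says that turnstile data are collected "for all members, when the following condition is present": "a) active payment + (b) a minimum of 1 attendance per month". A footnote is attached to this condition, but its text is not in the copy reviewed.

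Two other sections describe a wider population:
- Statistical methods: "Primary analyses will follow an intention-to-treat principle adapted to the cluster-allocated design", with eligible individuals analysed under their center's condition "regardless of attendance patterns or dropout".
- Sample size: "all eligible members of the participating fitness centers will be included in the analyses at three, six, nine, and 12 months".

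Eligibility criteria sets no minimum attendance for the primary outcome.

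On dropout, Statistical methods says "Dropout (membership cancellation) will be examined using administrative records from all members enrolling after September 1, 2025". Outcomes and the attrition formula count cancellations or dropouts, as if the two could differ.

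**The concern.** A month without a visit is the worst value that attendance can take, and it arises after the clubs were allocated. A rule that keeps data only where there was at least one visit selects on the outcome itself. The turnstile record shows that the true value is zero. It is not unknown, and it is removed because it is zero, so a missing-at-random argument does not cover it.

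The trial asks whether training staff helps members keep coming. If members who stop coming leave the data, the reported trajectories describe continuing attenders only, while the report calls them intention-to-treat. A training that turns non-attenders into occasional attenders would add low values to its own arm and gain nothing for the zeros it prevented.

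A paying member who stops coming may also be missed by the dropout outcome if dropout means cancellation only.

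**Working it through.** The protocol gives no attendance mean, spread or share of non-attending members, and no power calculation for attendance. There is no figure to reproduce, so the passages are compared first and the size is then shown under stated assumptions.

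**1. The passages side by side.** Under the collection rule, inclusion depends on attendance. Under Statistical methods it does not, and under Sample size all eligible members are present at each time point. Nothing shown says that an unvisited month is scored as zero.

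**2. What is lost under each reading.**
- *Mildest:* visits are divided by all weeks of the quarter, so a single zero month still pulls the mean down. Only quarters with no visits disappear.
- *Month removed:* zero months leave both numerator and denominator.
- *All three months must qualify:* the lowest possible value is 3 visits / 13 weeks = 0.23 visits/week, although true attendance can be 0.
- *Member removed:* at least as much is lost as when quarters are removed.

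All-zero quarters are lost in every case.

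**3. Small end (mildest reading, independent zero months).** Assumed: 1.24 visits/week in months with a visit, in both arms; zero months 25% (control) and 15% (intervention) of active member-months.
- Zeros counted: 1.24 × 0.75 = 0.930 and 1.24 × 0.85 = 1.054; difference 0.124.
- All-zero quarters: 0.25³ = 1.6% and 0.15³ = 0.3%.
- After removal: 0.930 / 0.9844 = 0.945 and 1.054 / 0.9966 = 1.058; difference 0.113.
- Retained: 0.113 / 0.124 = 91%, so about 10% is lost.

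**4. Large end (persistent lapses).**
- With the step 3 shares but fully persistent zeros, the means after removal are 0.930 / 0.75 = 1.24 and 1.054 / 0.85 = 1.24; difference 0.
- A mixed-model simulation (3,000 members per arm, gamma-distributed rates with mean 1.5 visits/week, the same 25% and 15%) gave at months 10–12 a difference of +0.129 (SE 0.014) with zeros counted and 0.000 (SE 0.012) with the filter. The control level rose from 0.924 to 1.239 (+34%).
- A gamma-Poisson simulation varied the inputs: attenders at 1.0, 1.5 or 2.0 visits/week, shape 0.8 or 1.5, and 30–40% of control members against 20% of intervention members without visits in the quarter. Differences of +0.10 to +0.40 fell to between −0.005 and +0.006, whether the filter worked by month or required all three months.
- The mildest reading gives the same result here. With attenders at 1.5 visits/week, shape 1.5 and lapses of 40% against 20%, the full means are 0.902 and 1.201, and the shares with any visit are 0.589 and 0.786. Then 0.902 / 0.589 = 1.53 and 1.201 / 0.786 = 1.53.

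**5. Sign reversal.** Assumed: 40% of each arm lapses, attenders average 1.5 visits/week (shape 1.5), and the intervention turns half of its lapsed members into low-frequency attenders.

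| Rate of rescued members (visits/week) | Zeros counted | Month filter | All three months required |
|---|---|---|---|
| 0.30 | +0.060 | −0.283 | −0.173 |
| 0.50 | +0.104 | −0.249 | −0.256 |
| 0.75 | +0.150 | −0.197 | −0.251 |

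The mildest reading reverses too. At 0.50 visits/week, rescued members have no visit in 13 weeks with probability e^(−6.5) = 0.0015, so the intervention share with any visit is 0.589 + 0.20 × 0.9985 = 0.789. Then 0.899 / 0.589 = 1.526 and 1.003 / 0.789 = 1.271, a difference of −0.255.

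**The case against.** **The footnote is not visible.** It is attached to the disputed words and could define an active user or an exception. This stands as a caveat. The main-text sentence still makes a monthly visit a condition for collecting data, so the footnote must be reconciled with Statistical methods.

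**The intention-to-treat sentence may only assign people to arms.** A member with some qualifying months stays in the analysis under the assigned condition, and the model uses whatever observations are available. This is partly right: on the mildest reading most members remain. It does not cover members who never attend or quarters without visits, and the sentence expressly sets attendance patterns aside.

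**Between-condition comparisons are declared exploratory and descriptive**, with one center per condition. That is so, and no confirmatory test is at stake. The plan still puts its emphasis on the magnitude and direction of the trajectories, which the filter can change.

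**Two stronger readings are tempting.**
- A reader might infer that the filter must erase the effect. The documents do not support this. The complete loss in step 4 follows from letting the arms differ only in their share of zeros. Step 3 shows a small loss under other assumptions.
- A reader might infer that a paying member who stops coming is counted as a failure nowhere. Outcomes and the attrition formula name dropouts alongside cancellations, so such a member may be counted there. What is established is that the definitions differ.

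**Conclusion.** The point holds as a contradiction in the protocol. The collection rule conditions the primary outcome on its own post-allocation value and conflicts with both Statistical methods and Sample size. On the visible wording, every reading loses at least the quarters without visits, and missing at random does not cover that loss.

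Mean attendance is overstated in every arm: in the control arm of the examples, from under 2% (0.930 to 0.945) to about a third (0.924 to 1.239). The bias in differences between conditions runs from about 10% of the difference to all of it, with a sign reversal if lapsed members become low-frequency attenders. These sizes rest on assumed attendance rates and lapse patterns, and the documents do not show which pattern applies. That a lapsed paying member may also be missed by the dropout outcome is a possibility arising from inconsistent definitions and is not established.

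**What to change.** 1. Remove the one-visit-per-month condition from the primary attendance dataset. Include every eligible member, score weeks or months without a turnstile entry during active membership as zero, and put all weeks of the interval under active membership in the denominator.
2. State how months after cancellation are handled, so that this agrees with the intention-to-treat sentence, which also sets dropout aside. Removing the visit condition alone leaves the active-payment condition in place, and those months would still vanish. One option is to count them as zero visits, with their weeks in the denominator, in the primary analysis, and to use while-a-member attendance as a sensitivity analysis.
3. Use one definition of dropout in Outcomes, in the attrition formula and in Statistical methods, and say whether a paying member who stops coming is included.
4. If the one-visit rule is wanted, keep it only for a labelled supplementary description of active users. Report the share of zero-visit months by club.
5. Bring the footnote to the condition into line with these changes.

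The cost is a change of wording, a re-run of the electronic extract and lower mean attendance figures. No new data collection is needed.

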As for the secondary outcomes, these will focus on (i) dropout rates at three-month intervals up until one year, and (ii) motivational variables. In the case of dropout rates, administrative records from all members enrolling after September 1, 2025, will be used. This outcome is derived from the complete population of new members during the intervention period, and the expected number of observed events over the 12-month follow-up is sufficient to support descriptive and time-to-event analyses of attrition patterns across intervention conditions. In the case of the motivational variables, the most restrictive analyses will be conducted in a subsample of exercisers enrolling in September. These participants will be recruited for the longitudinal assessment of behavioral regulation, satisfaction of basic psychological needs, exercise enjoyment, subjective exercise experience, exercise habit, and intention to be physically active, assessed at baseline, six months, and twelve months. Sample size considerations for this subsample were guided by the most restrictive planned within-participant longitudinal comparisons and estimated using G*Power (v.3.1.9.7) (Faul et al., 2009). Using benchmarks from a related work [e.g. (Teixeira et al., 2023; Andrade et al., 2022; Henriques et al., 2023)], a repeated-measures ANOVA assuming a small-to-moderate magnitude of change over time (*f* = 0.20), an *α* level of 0.05, statistical power (1-*β*) of 0.95, three repeated measurements, a correlation between repeated measurements of approximately r = 0.70, and allowing for potential violations of sphericity (*ε* ≈ 0.70), a minimum of approximately 53 participants completing follow-up assessments across the three fitness centers is expected to provide adequate sensitivity to characterize meaningful longitudinal changes in motivational outcomes over time. Linear mixed-effects models will be used for analysis, as they are expected to be at least as efficient as the repeated-measures assumptions used for these calculations and allow the inclusion of all available data in the presence of missing observations. Given that the average attrition rate in Portugal over a one-year period in these contexts has been reported as ranging between 50 and 60% (Pedragosa and Ferreira, 2024), a total sample of approximately 117 participants (≈55% attrition) will be required.

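### The attrition rate has two different denominators, and a crude whole-season percentage among new members counts late joiners who were hardly at risk

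*Protocol article*

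**What the plan says.** Four places in the protocol article bear on this.

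- **Outcomes** makes attrition a secondary outcome, with cancellations or dropouts expressed "as a percentage of the total number of new members in a given time period". It refers the reader to the Methods for details. New members are those who enrol between 1 September 2025 and 31 August 2026.
- **Club attendance and attrition rate** prints the formula: "Number of Cancellations or Dropouts / Total Number of Members", times 100. On its use: "The attrition rate will be calculated for each 3-month period and the entire season with the following formula". It then adds: "New club members who enrolled in the fitness clubs after September 1, 2025, will also be identified separately for subgroup analysis". The formula is thus for all members first, with new members as a subgroup.
- **Sample size** says that for dropout "administrative records from all members enrolling after September 1, 2025, will be used". It also gives the scale: "Each participating fitness center has more than 2,000 enrolled members at any given time", and about 200 joiners per club in September.
- **Statistical methods** again limits dropout to members joining after 1 September 2025 and glosses it as membership cancellation. It states: "Percentage attrition rates will be reported descriptively". Kaplan-Meier curves are added to show when dropout occurs, and members still enrolled are censored. The time origin of the curves is not stated.

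Secondary hypothesis (a) in Objectives is that both training conditions will have lower attrition rates than control.

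**The concern.** There are two separate problems.

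First, the outcome definition and the printed formula describe different populations. One analyst following Outcomes and another following the formula would report different numbers under the same name, and either could be set against hypothesis (a).

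Second, neither definition uses members at risk or person-time. A member who joins in August 2026 has at most a month in which to cancel, but counts in the season denominator as much as someone who joined on the first day. The crude season percentage therefore falls below 12-month attrition, by an amount that depends on when people joined. There is one club per condition, so a difference in enrolment timing between clubs cannot be separated from a difference between conditions.

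**Working it through.** **The plan's own figures.** The protocol projects no attrition percentage under either definition, so there is none to reproduce. Its only related arithmetic is the inflation of 53 completers for about 55% attrition: 53 / (1 − 0.55) = 117.8, against a stated 117. That figure is not affected by this point. I take 55% as 12-month attrition because it is the value used there, with the range of 50–60% quoted in Sample size.

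**Inputs from the protocol:** 2,000 members per club, 200 September joiners, 12-month attrition A = 55% (50–60%), entry open for 12 months.

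**Assumptions, not in the protocol:** a constant cancellation hazard, entry spread evenly within each period, and n joiners in each month from October to August.

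**Step 1, hazard.** h = −ln(1 − A)/12 = −ln(0.45)/12 = 0.0665 per month.

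**Step 2, expected proportion cancelled by 31 August 2026.** For follow-up spread evenly from a to b months, it is 1 − [exp(−ha) − exp(−hb)] / [h(b − a)].

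- September joiners (11 to 12 months): 53.5%
- October to August joiners (0 to 11 months): 29.1%
- Joiners in the last three months (0 to 3 months): about 9.4%
- Uniform entry over the season (0 to 12 months): 31.1% (27.9% at A = 50%, 34.5% at A = 60%)

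**Step 3, crude season percentage among new members.** This is (200 × 0.535 + 11n × 0.291) / (200 + 11n), computed with unrounded proportions.

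| n per later month | New members | Crude % at A = 55% | Range, A = 50–60% |
|---|---|---|---|
| 20 | 420 | 40.7 | 36.7–44.8 |
| 50 | 750 | 35.6 | 32.0–39.3 |
| 100 | 1,300 | 32.8 | 29.5–36.4 |
| 200 | 2,400 | 31.1 | 27.9–34.5 |

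All are well below the 55% that generated them.

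**Step 4, two clubs with the same hazard (A = 55%).**

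| Later joiners per month | Crude % | Gap (points) |
|---|---|---|
| 90 vs 110 | 33.2 vs 32.6 | 0.6 |
| 80 vs 120 | 33.6 vs 32.3 | 1.3 |
| 30 vs 150 | 38.3 vs 31.7 | 6.6 |
| 20 vs 100 | 40.7 vs 32.8 | 7.9 |

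**Step 5, new-member rate against all-member rate.** Take n = 50, so about 267 cancellations among 750 new members, or 35.6%. For the all-member formula, add 2,000 existing members with an assumed season attrition of 20% to 55%:

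- (2,000 × 0.20 + 267) / 2,750 = 24.3%
- (2,000 × 0.55 + 267) / 2,750 = 49.7%

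The all-member rate can fall on either side of the new-member rate, and it is driven mainly by people who joined before the training.

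**Step 6, Kaplan-Meier by time since enrolment.** In 400 simulated seasons per setting, the 11-month estimate averaged 52.0% at n = 20 and 51.8% at n = 100. The true value is 1 − exp(−11h) = 51.9%. The estimator does not depend on enrolment flow. At 11 months about 200 × (1 − 0.519) = 96 September joiners per club would still be at risk. At 12 months almost nobody would be, because observation ends on 31 August 2026.

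**The case against.** The other side has a good deal to say.

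- **The definitions are nearly reconcilable.** Outcomes, Sample size and Statistical methods all point to new members, and the formula section names them as a subgroup. This stands in part: one section is out of line with three. It is nonetheless the section with the formula, and the one to which Outcomes appears to send the reader.
- **Unequal follow-up is already handled.** Censored time-to-event analysis is planned, and between-condition comparisons are called exploratory and descriptive. This also stands in part. The curves are sound if time runs from enrolment, but their stated use is to show timing. The percentages are what is reported as attrition, and hypothesis (a) is directional. A descriptive figure still needs one definition.
- **The clubs are alike.** Trial setting and the recruitment section describe similar centres with standardized practices, and September intake is about 200 in each. If later flow is also alike, the gap between clubs is around a point or less. The understatement of 12-month attrition remains.

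A reader might infer more than the text supports in three ways:

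- **A tenfold discrepancy**, with 100 cancellations being 50% of 200 or 5% of 2,000. This keeps the numerator fixed while the population changes. The protocol nowhere says to divide new-member cancellations by all members, and Step 5 shows the more natural comparison.
- **Quarterly rates above 100%.** This needs the most literal reading of Outcomes, with a quarter's cancellations over that same quarter's joiners. Even then, with new-member cancellations only and 20 to 100 joiners per later month, later quarters come to about 31% to 81%.
- **Conflicting numerators.** Cancellation and dropout are named together in two places, and one is glossed as the other in a third. That reads as one event under two names.

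**Conclusion.** The point holds in a limited form and should be corrected. The conflict in denominators is plain in the text and depends on no assumption. The crude season percentage among new members would understate 12-month attrition: about 31% against 55% with uniform entry, and 31–41% with 200 September joiners plus 20 to 200 per later month. These sizes rest on a constant hazard and an assumed later flow. The direction needs only that some joiners are followed for less than a year and could still have cancelled within it.

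The artificial gap between clubs is less certain. It runs from about 1 point to 7 or 8 points over the flows tried, and would vanish if enrolment patterns matched. The protocol gives no later flow, so it does not support a claim that enrolment will in fact produce an apparent effect. The Kaplan-Meier curves, the attendance analysis and the 53 and 117 figures are not called into question.

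**What to change.** In Outcomes, Club attendance and attrition rate, and Statistical methods, use one definition of attrition for hypothesis (a): 1 minus the planned Kaplan-Meier estimate of membership cancellation among members joining from 1 September 2025, with time measured from enrolment.

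- Report it with numbers at risk at 3, 6 and 9 months, and at the latest time with adequate numbers at risk. That is about 11 months; a 12-month value would have almost no one behind it.
- Restrict any crude season percentage to the September cohort, whose members all have 11 to 12 months of possible follow-up.
- For 3-month rates, use members at risk at the start of each interval as the denominator.
- Keep the all-member rate as a separately named club-level descriptor, for comparison with the pre-intervention year that Outcomes lists among its additional variables.

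The cost is rewording three sections and slightly more analysis. Enrolment and cancellation dates are already needed for the planned curves, so no new data are required.
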